#### Acceptability and Feasibility Study

To evaluate the acceptability and effectiveness of NeW-I, all intervention participants are invited to participate in a semistructured interview at the completion of all intervention components at time point 2, which explores the impact of the intervention, aspects of the intervention found to be helpful, aspects of the intervention found to be unhelpful and how they could be improved, challenges encountered in completing the intervention, and scope for enhancing intervention usability. To assess the feasibility of implementing and delivering NeW-I, the research team maintains an audit trail of the time needed to provide feedback to participants and restructure their narrative writing; deviations from the intervention protocol (if any); uncompleted interventions and their reasons; and NeW-I therapists’ perceptions of competence, observations of participants’ experiences and responses, and difficult or deviant cases. All feedback provided to participants will be vetted by at least two members of the research team for data monitoring, quality, and safety assurance.

### Data Analysis

#### Quantitative Data

The statistical analysis plan for the quantitative data in this study was designed according to the Consolidated Standards of Reporting Trials guidelines [64] and recommendations made by Gamble et al [65] for clinical trials. Quantitative parameters will be presented as mean (SD) or median (IQR), and categorical variables will be presented as numbers and proportions. The internal consistency of psychometric scales will be assessed using Cronbach alpha. To compare the primary quantitative outcome (KQOL) and secondary quantitative outcomes (FACIT-Sp-12, HHI, PHQ-9, BSFC-s, ISS, and BGQ) between the intervention and control groups over time (time point 1 to time point 5, with time point 2 being the primary time point of comparison), multilevel mixed-effect regression analysis will be used with time as a random effect. All demographic and other relevant covariates measured at baseline will be adjusted in the model. Mixed models allow us to include all available data in the presence of dropouts occurring into the analysis [66]. Individual multivariable models will be constructed for each outcome to estimate the effect sizes and corresponding CIs. Clinically meaningful interactions will also be checked and included in the model if *P*<.10. Marginal effects will be used to predict mean outcome scores for the intervention and control groups. For this study, a two-sided significance level of at least .05 will be considered a statistically significant finding. All analyses will be conducted using Statistical Package for the Social Sciences (SPSS) (version 22.0; IBM Corp) and Stata (version 15.1; StataCorp) statistical software.

The intention-to-treat principle will be followed in the data analysis. However, an additional sensitivity analysis will be conducted to handle missing data during the analysis, where fully conditional multiple imputation with *n (% missing)* imputations and 1000 iterations using the Markov Chain Monte Carlo method will be used [67]. Model summary estimates will be calculated based on the Rubin rule [68].

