Following this, participants are directed to a screening page where participants complete the PHQ-9 and the K-10. Those who pass the screening assessments receive confirmation of study participation and are requested to wait for a phone call from the research team. Those who do not pass the screening assessments are thanked for their time and provided with resources for psychosocial support. Individuals who pass the screening assessments receive a phone call from the NeW-I team as a means of identity checking. Following this, participants complete baseline measures (time point 1 assessment). This is followed by a random allocation of participants to either the intervention group or the control group, which is performed via the NeW-I platform using computer-generated random numbers. Participants are then directed to the first writing session. Participants have the option to choose to begin the first writing session immediately or delay for a maximum of 3 days. The day on which participants begin their first writing session is day 1 of week 1. Participants who do not begin their first writing session within 3 days are excluded from the study. However, a concession period of 7 days is given to participants who have a genuine reason for their inability to adhere to the protocol (such as unexpected changes in their child’s health condition) and have expressed keen interest in participating in the study. A similar concession period of 7 days is also maintained for participants who are unable to adhere to the study protocol in weeks 2, 3, and 4 (such that each participant can only be given 1 concession during the entire duration of their study participation). Detailed study procedures are described in Figure 2.

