### Evaluation of Outcomes

#### Quantitative Assessments

Via the NeW-I platform, both intervention and control group participants fill out a sociodemographic form at baseline and are then assessed on a battery of self-reported standardized and validated measures across 5 time points. The primary outcome measure is the participants’ quality of life, as measured by the Kemp Quality of Life scale (KQOL) [58]. Secondary outcomes are assessed using (1) a modified version of the Functional Assessment of Chronic Illness Therapy - Spiritual Well-Being scale (FACIT-Sp-12) [59], (2) the Herth Hope Index (HHI) [60], (3) Patient Health Questionnaire – 9 [53], (4) the Burden Scale for Family Caregivers-Short (BSFC-s) [61], (5) the Inventory of Social Support (ISS) [62], and (6) a modified version of the Brief Grief Questionnaire (BGQ) [63] (Table 4).

**Table 4 table4:** Quantitative outcome measures.

Measure	Number of items	Rating scale; factor
Kemp Quality of Life scale	1	7-point Likert scale; 1 factor
Functional Assessment of Chronic Illness Therapy - Spiritual Well-Being (adapted version)	12	5-point Likert scale; 3 factors: meaning, peace, and faith
Herth hope index	12	4-point Likert scale; 1 factor
Patient Health Questionnaire - 9 (also serves as a screening assessment)	9	4-point Likert scale; 1 factor
Burden Scale for Family Caregivers-Short	10	4-point Likert scale; 1 factor
Inventory of Social Support	5	5-point Likert scale; 1 factor
Brief Grief Questionnaire (adapted version)	5	3-point Likert scale; 1 factor

Assessment for both intervention and control groups takes place at 5 time points: baseline (time point 1), immediately after completion of the intervention or control protocol (time point 2), 1 month after completion of the intervention or control protocol (time point 3), 3 months after completion of the intervention or control protocol (time point 4), and a final follow-up 6 months after completion of the intervention or control protocol (time point 5). Participants receive an automated notification on their phone app and email each time an assessment set becomes available to them. For each completed assessment, participants receive a voucher worth Singapore $30 (approximately US $21).

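### The stated primary model does not guarantee an estimate of the group difference at time point 2, the declared primary time point

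*Protocol article*

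**What the plan says.** Under Data Analysis, Quantitative Data, the protocol article compares the groups on KQOL and the secondary outcomes over "time point 1 to time point 5, with time point 2 being the primary time point of comparison". For this, "multilevel mixed-effect regression analysis will be used with time as a random effect". The same paragraph adds:

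- on covariates: "All demographic and other relevant covariates measured at baseline will be adjusted in the model". Baseline KQOL is not named, and time point 1 is listed among the outcome times.
- on interactions: "Clinically meaningful interactions will also be checked and included in the model if" P<.10. Which interactions are meant is not said.
- on group means: "Marginal effects will be used to predict mean outcome scores for the intervention and control groups". No time point is attached.

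Under App and Intervention Procedure, baseline measures are completed first, and then: "This is followed by a random allocation of participants to either the intervention group or the control group". Time point 1 is therefore a pre-randomisation value.

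**The concern.** A group difference at one visit is a parameter of a longitudinal model only if that model lets the difference vary by visit, which requires a group-by-time term. The paragraph names no such term. It gives time a random role, and the one rule it states for interactions makes their entry depend on a significance test.

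Without group-by-time, the model has a single group coefficient that applies to every visit. Predicted group means then show the same gap at every time point, so marginal effects cannot recover a time point 2 difference. Because time point 1 is among the outcomes and its expected difference is zero, it pulls that coefficient towards zero.

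The primary estimate is at stake, and it is meant to inform a full-scale protocol. The Discussion also promises to evaluate whether benefits last, which is itself a group-by-time question.

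**Working it through.** **Inputs from the protocol article.** Five assessments, the first before randomisation; primary comparison at time point 2; planning effect 0.2 SD; 25 per arm before attrition. The article's own sample size reproduces: 25/(1 − 0.3) = 35.7, rounded up to 36 per arm and 72 in total.

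**Inputs assumed, because the article does not give them.** Complete data, a random intercept, within-person correlation 0.5 to 0.7, and the course of the effect over time.

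**Step 1: the group coefficient without group-by-time.** Under a random intercept with complete data, generalised least squares gives each of the five visits weight 1/5. The coefficient, as a fraction of the time point 2 effect, is the mean of the effect profile over time points 1 to 5:

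| Assumed course | Profile | Fraction | If the time point 2 effect is 0.20 |
|---|---|---|---|
| Constant | 0, 1, 1, 1, 1 | 4/5 = 0.80 | 0.16 |
| Milder fade | 0, 1, 0.75, 0.5, 0.25 | 2.5/5 = 0.50 | 0.10 |
| Steeper fade | 0, 1, 0.5, 0.25, 0 | 1.75/5 = 0.35 | 0.07 |

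Adding a random time slope does not remove the dilution. With assessments at an assumed 0, 1, 2, 4 and 7 months and slope variance 0.002 to 0.01, baseline takes 23% to 30% of the weight, and a constant effect shrinks to 0.77 to 0.70 of its value.

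**Step 2: how often the screen would admit group-by-time.** For a 4-df test at P<.10 the non-centrality is λ = n·d²·Q / [2(1 − ρ)], where n is the number per arm and Q is the sum of squares of the profile about its own mean.

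- Constant: Q = 4 − 4²/5 = 0.80.
- Milder fade: Q = 1.875 − 2.5²/5 = 0.625.

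Lowest case (n = 25, ρ = 0.5, milder fade): λ = 25 × 0.04 × 0.625 / 1 = 0.625, giving a 15% chance of entry. Highest case (n = 36, ρ = 0.7, constant): λ = 36 × 0.04 × 0.80 / 0.6 = 1.92, giving 26%. At the planning effect the term would therefore usually be left out.

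**Step 3: the two-step rule as a whole.** Report the time point 2 contrast if the term enters, and the averaged coefficient otherwise. In 20,000 simulated trials with 25 per arm, correlation 0.5 and a true time point 2 effect of 0.20, the mean reported estimate was about 0.17 (constant) or 0.13 (milder fade). With no true effect, nominal 5% testing rejected in 5.6% and 6.2% of trials in two runs of the same null case.

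**Step 4: with group-by-time always kept.** The time point 2 contrast is unbiased under each of these courses: 0.20 stays 0.20.

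**The case against.** The strongest defence is that this is a condensed sentence with a sound reading. Time as a random effect may be shorthand for a random slope beside a fixed time effect. A multilevel model already implies visits nested in participants. Naming a primary time point within a comparison over time makes sense only if visit-specific contrasts are intended, and marginal effects could be computed at each visit. The interaction sentence does not mention group-by-time; its wording could refer to treatment-by-covariate terms added to the main comparison. A fuller analysis plan may spell all this out.

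Much of that stands. A reader might infer that the planned model can never estimate the time point 2 difference, or that the reported effect will be about a third of the true one. The document supports neither. The first ignores the compatible reading. The second takes the steeper assumed fade and supposes that group-by-time is always omitted. The average loss under the two-step rule, 0.03 (0.20 − 0.17) to 0.07 (0.20 − 0.13), is also small beside the standard error of an unadjusted standardised difference with 25 per arm, √(2/25) = 0.28.

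What does not stand is that this is only a detail left to another document. The article itself states the outcome visits, the role of time, the primary visit and the interaction rule, and it does not exempt group-by-time from that rule. Two analysts following the text could fit different models with different primary parameters.

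**Conclusion.** The primary model is badly fixed: as stated, it does not guarantee an estimate at the declared primary time point. If group-by-time is subject to the screen and left out, the group coefficient is 0.80 of a constant effect, or 0.35 to 0.50 of the time point 2 effect under the assumed fades. If the screen decides, the estimand depends on the data, and entry is unlikely (15% to 26%) at the planning effect. The average bias of the two-step rule is more modest, and inflation of the type I error is slight.

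The dilution requires the interaction to be omitted and baseline to be among the outcomes. Its size rests on an assumed effect course, correlation and covariance structure and on complete data. The point is a conflict among stated elements that needs resolving, not proof that the time point 2 contrast is out of reach.

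**What to change.** State the primary model in full:

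- outcomes: KQOL at time points 2 to 5 with baseline KQOL as a covariate, or all five time points with baseline means constrained equal between groups;
- fixed effects: group, categorical time, and group-by-time kept whatever its P value, plus the chosen baseline covariates;
- random part: participant as the random unit; a random time slope may be added;
- primary estimate: the group contrast at time point 2 with its confidence interval, and marginal means reported by group and time point;
- P<.10 screen: limited to exploratory interactions other than group-by-time.

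The cost is a few sentences and one changed model command, settled before the outcome data are analysed. No new data or design change is needed.

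### Letting interactions with P<.10 into every outcome model, primary KQOL included, makes the treatment effect at time point 2 depend on a data-driven selection that its P value and CI ignore

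*Protocol article*

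**What the plan says.** The relevant text is in the Protocol article, Data Analysis, Quantitative Data.

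- **Model.** For the between-group comparison, "multilevel mixed-effect regression analysis will be used with time as a random effect". It runs over time points 1 to 5, "with time point 2 being the primary time point of comparison".
- **Covariates.** "All demographic and other relevant covariates measured at baseline will be adjusted in the model". The article gives no number or list.
- **Scope.** "Individual multivariable models will be constructed for each outcome to estimate the effect sizes and corresponding CIs". There are seven outcomes, KQOL (primary) and six secondary.
- **Interaction rule.** "Clinically meaningful interactions will also be checked and included in the model", on the condition that P<.10. The candidates are not named.
- **Reading the result.** "Marginal effects will be used to predict mean outcome scores for the intervention and control groups".
- **Dropouts.** "Mixed models allow us to include all available data in the presence of dropouts occurring into the analysis".

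The Sample Size Calculation section starts from 25 per arm and enrols 36 per arm to allow for 30% attrition at follow-up.

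**The concern.** The article places a model-building step inside the confirmatory model. Whether an interaction is in the final KQOL model is decided by its P value in the same data that then supply the treatment effect, its CI and its test. The plan does not say that the primary comparison is taken from a model fixed before this step, and it describes no correction for the selection.

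Two consequences follow if a group-by-covariate term enters. The group coefficient changes meaning: it becomes the effect at the reference level of whichever covariate was selected. Its nominal 5% test and 95% CI also take no account of the selection. Because each outcome has its own model, different terms may be kept for different outcomes, and the seven effects may then not be the same kind of quantity. The article says the pilot's results will inform a full-scale protocol, so an effect estimate with understated uncertainty would be carried forward.

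A fuller analysis plan that named the candidate interactions would not remove the problem, because entry would still be decided by P<.10.

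**Working it through.** **1. The plan's own figure.** 25/(1 − 0.3) = 35.7, rounded up to 36 per arm and 72 in total. This reproduces. Expected at follow-up: 72 × 0.7 = 50.4, about 25 per arm.

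**2. Chance that at least one null interaction enters.** For m independent candidates at P<.10 this is 1 − 0.9^m:

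| m | 3 | 6 | 10 | 12 |
|---|---|---|---|---|
| chance | 27% | 47% | 65% | 72% |

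The values of m are assumptions, since the article names no candidates. Simulation with 6 to 12 candidates gives 47% to 72%.

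**3. Type I error after selection, single time point.** Set-up: linear model at one time point as a stand-in for the mixed model, 25 per arm, no true effect, all k covariates entered, each group-by-covariate term kept if P<.10, nominal 5%, t-based tests.

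| Candidates | Group coefficient | Marginal (averaged) effect |
|---|---|---|
| 3 | about 7% | – |
| 6 to 12 (mixed binary and continuous) | 9.7% to 16.4% | 5.2% to 6.9% |
| 5 (all binary) | 10% to 12% | about 6% |
| 10 (all binary) | about 16% | about 6% |
| 15 (all binary) | 19% to 20% | 7.5% to 8% |

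With 4000 runs the Monte Carlo SE near 5% is √(0.05 × 0.95/4000) = 0.34 points, so 5.2% cannot be told apart from 5%. With 72 parents and 5 to 15 binary candidates, the coefficient reading still gives 10.5% to 21% and the marginal reading 4.5% to 7%. The inflation depends on where the coefficient is read: with ten continuous covariates at n=50 it was 6.7% on either reading.

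**4. Type I error if the effect is a group-by-time contrast at time point 2.** Set-up: five time points, intraclass correlation 0.5 (assumed and treated as known), non-prognostic covariates, group-by-covariate terms kept at P<.10, 1500 runs.

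| Data | k | No covariates | After selection |
|---|---|---|---|
| 50 complete | 6 | 5.3% | 5.5% |
| 50 complete | 12 | 4.2% | 4.3% |
| 72 with 30% dropout | 6 | 4.9% | 4.9% |
| 72 with 30% dropout | 12 | 6.1% | 6.3% |

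Interactions entered in 43% to 68% of runs, yet the contrast hardly changed. Its variance ratio against no covariates was 1.000 to 1.006. Time-constant covariates and two-way group-by-covariate terms barely touch a within-person change.

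**5. Covariate adjustment alone, without selection.** At n=50, k=5 to 15, t-based type I error was 4.6% to 5.6%. For k uninformative covariates the SE multiplier is √((n − 3)/(n − k − 3)), and adjustment breaks even when the covariates explain R² = k/(n − 3):

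| k | SE multiplier, R²=0 | Break-even R² | Simulated SE ratio, R²=0.3 |
|---|---|---|---|
| 5 | √(47/42) = 1.06 | 5/47 = 0.11 | 0.88 |
| 10 | √(47/37) = 1.13 | 10/47 = 0.21 | 0.94 |
| 15 | √(47/32) = 1.21 | 15/47 = 0.32 | 1.01 |

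Precision can therefore be gained or lost. The article gives neither k nor R².

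**The case against.** The strongest case against the point is that the harm depends on choices the article does not make.

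- The rule is limited to clinically meaningful interactions, which may be few. It does not say that they are group-by-covariate, and group-by-time would be a natural candidate.
- Marginal effects are named for the group means, and on that reading the inflation is small.
- The planned model is longitudinal with baseline in the outcome series. If the effect is read as group-by-time, step 4 shows almost no damage.
- About 50 is the number expected after 30% attrition at follow-up. Time point 2 comes straight after the four weekly sessions and all available data are used, so between 50 and 72 parents may contribute.

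All of this stands, and it limits the size of the problem. It does not remove the rule. The article assigns marginal effects to predicting mean scores but says the multivariable models supply the effect sizes and CIs, so the conditional coefficient remains a possible reading.

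A reader might go further and infer that the primary model is overfitted, that full adjustment loses precision, or that the error rate certainly exceeds 5%. The documents do not support these. The number of covariates is not given, prognostic covariates can improve precision, adjustment alone holds 5% with t-based tests, and the tested quantity is not stated. A covariate list may also sit in the full analysis plan, so its absence from the article is not the fault.

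**Conclusion.** The point holds in a limited form. The article writes a P<.10 inclusion rule into the model for every outcome and does not keep the primary time point 2 comparison apart from it, so the reported effect and its CI can rest on an unacknowledged selection.

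At 25 per arm, type I error is about 7% (3 candidates) to 10% to 16% (6 to 12 candidates) if the conditional group coefficient is read after a group-by-covariate term enters. It is about 5% to 7% if the marginal effect is tested, and close to nominal for a group-by-time contrast. These figures rest on assumed candidate counts, on null and mostly non-prognostic covariates, and, except for the last, on a single-time-point stand-in for the mixed model.

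The broad covariate adjustment is a risk to precision, not a demonstrated fault. The change is worth making because it costs almost nothing and removes the dependence on which reading is chosen.

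**What to change.** 1. Define the primary contrast as the group difference in KQOL at time point 2, estimated from a model fixed before the data are seen. Baseline KQOL should be accounted for, the covariates should be a short, named, prognostic set, and no interaction should be chosen by its P value.
2. Delete the P<.10 inclusion rule from the primary and secondary models, so that all seven outcomes are analysed in the same form.
3. Report group-by-covariate interactions separately, as exploratory estimates with CIs.
4. Keep the fuller covariate model, if wanted, as a sensitivity analysis.

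With a fixed model and t-based inference, simulated type I error at n=50 is 4.6% to 5.6%. Holding the list to five covariates caps the worst-case SE loss at about 6%, against 13% with ten and 21% with fifteen.

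The cost is a change of wording. The small downside is less adjustment for chance imbalance in the other demographics, which the sensitivity model covers. N stays at 72.

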#### Qualitative Data

All qualitative data are stored and analyzed using the NVivo (QSR International) computer software. Phenomenological analysis will be used to obtain an in-depth and comprehensive view of the data set from an insider’s perspective [69]. Unique or minority voices will be elicited to illuminate counterpoints to the stated views. Throughout the data analysis process, strategies to maximize research rigor and trustworthiness will be prioritized. The use of such a method of data analysis has been demonstrated in previous research involving grief therapy with bereaved parents [70].

